### Ethics and trial registration

The study is conducted in accordance with the Helsinki 2 declaration and has been approved by the Danish Research Ethics Committee in March 2008 (H-C-2007-0057). The study is registered at EUDRACT (European Union Drug Regulating Authorities Clinical Trials) and at clinicaltrials.gov (Identifier NCT01046942).

## Discussion

The evidence for clopidogrel in addition to aspirin after CABG is divergent, although most studies have not been able to demonstrate any beneficial effect of dual antiplatelet therapy. Meanwhile, emerging evidence from observational studies has demonstrated a significantly higher thromboembolic risk in both PCI and CABG patients that are TEG-Hypercoagulable. The TEG-CABG trial is the first randomized trial to investigate preoperatively TEG-Hypercoagulable CABG patients. The rationale being that this is a patient population with a heightened thromboembolic risk (including graft occlusion) due to the hypercoagulability, but, hence, also is at low risk for bleeding on dual antiplatelet therapy. We hypothesize that this subgroup of CABG patients will benefit the most on a dual antiplatelet regimen both in regards to SVG patency and thromboembolic complications in general.

Examining hemostatic ability and status before and after surgery/intervention with TEG, we believe will be the future for postoperative thromboembolic risk evaluation. Including Multiplate aggregometry measurements in our trial will also help elucidate if resistance measurements after cardiac surgery can help better tailor antiplatelet regimens. These points become even more important as the patients referred to cardiac surgery get older and have more co-morbidities, and, hence, have limited physiological reserves, where graft occlusions and even small thromboembolic episodes can have detrimental effects on overall health and survival.

### Limitations

Due to lack of funding no placebo drug is used, and this is why the open label design was chosen. However, we find it plausible to assume that the primary endpoint of graft patency after three months will not be affected by the lack of placebo drug in the control group, as the MSCT evaluators are blinded.

## Conclusions

The TEG-CABG trial is the first randomized trial to investigate whether TEG-Hypercoagulability, before and after CABG, is predictive of trombembolic events and death, and if intensified antiplatelet therapy can reduce this risk. The primary end-point will be SVG patency at three months postoperatively. The results of this study may help redefine how patients undergoing coronary surgery could be evaluated individually in the future for their postoperative thromboembolic risk, and enable clinicians to tailor antiplatelet therapy to counter this risk.

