**Figure 1 F1:**
[figure not shown]
Study flow chart.

The study nurse, utilizing the sealed envelope technique, randomizes 250 TEG-Hypercoagulable (TEG MA >69 mm) patients on the day before CABG, allocating 125 patients to the interventional group (receiving clopidogrel for three months and lifelong aspirin) and 125 TEG-Hypercoagulable patients to a control group (receiving lifelong aspirin only).

TEG, Multiplate aggregometry and routine blood samples are obtained the day before surgery, on Day 4 after CABG, and at three months postoperatively.

MSCT is conducted at three months after surgery.

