### Outcome measures

Primary:

Graft patency assessed at three months by MSCT will be significantly improved in TEG-Hypercoagulable patients allocated to dual antiplatelet therapy with clopidogrel and aspirin as compared to aspirin alone.

Secondary:

1. TEG-Hypercoagulable patients will suffer fewer thromboembolic events (that is, MI, stroke, pulmonary embolism, gastrointestinal ischemia, deep vein thrombosis) or cardiovascular death when on clopidogrel and aspirin vs. aspirin alone.

2. Assess if the degree of surgically induced hypercoagulability itself is an independent factor of graft occlusion, thromboembolic events and death.

3. High on-treatment platelet reactivity in spite of Aspirin and/or clopidogrel treatment, as evaluated by Multiplate aggregometry, increases the risk of thromboembolic events after CABG surgery.

All outcome measures will be evaluated at three months postoperatively.

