#### ***Improvement of graft patency from 80% to 90%: 219 grafts per group***

With an average of 2 SVGs per patient; 219/2 = 110 patients in each group.

We will include 125 patients in each group to account for “drop-outs” and be able to detect at a significance level of 5% or better.

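### The Conclusions say the trial tests preoperative TEG-hypercoagulability as a predictor, but every randomised patient is hypercoagulable; and secondary outcomes 2 and 3 let clinical events come before the marker

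*Protocol article*

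**What the plan says.** The Conclusions state: "The TEG-CABG trial is the first randomized trial to investigate whether TEG-Hypercoagulability, before and after CABG, is predictive of trombembolic events and death". The Discussion adds: "We hypothesize that this subgroup of CABG patients will benefit the most on a dual antiplatelet regimen".

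Under Design and randomization procedure, the study nurse "randomizes 250 TEG-Hypercoagulable (TEG MA >69 mm) patients on the day before CABG". The comparator is also hypercoagulable: "125 TEG-Hypercoagulable patients to a control group (receiving lifelong aspirin only").

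TEG and Multiplate samples are taken the day before surgery, then "on Day 4 after CABG, and at three months postoperatively". Under Outcome measures, secondary outcome 2 is to "Assess if the degree of surgically induced hypercoagulability itself is an independent factor of graft occlusion, thromboembolic events and death". Secondary outcome 3 states that high on-treatment platelet reactivity raises thromboembolic risk. The same section sets three months as the evaluation time for all outcomes, and Data collection says that in-hospital infarction and stroke are recorded.

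**The concern.** There are two separate problems.

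**Preoperative status.** A predictor has to vary. Preoperative hypercoagulability, as a yes/no status, is a condition of randomisation. A statement that the randomised trial investigates whether it predicts events promises a contrast that this cohort does not contain. Saying who benefits most needs still more: the clopidogrel effect in normocoagulable patients, and a comparison of the two effects. The use the article foresees for its results, individual risk evaluation and tailored antiplatelet therapy, leans on that contrast.

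**Marker timing.** A marker can predict only what happens after it is measured. The degree of surgically induced hypercoagulability and on-treatment reactivity both need a postoperative sample, while the outcome clock starts at surgery. If all events to three months are related to such a reading, some come before it, and patients who die early have no reading at all. The resulting association would not be a prediction, although outcome 3 is worded as a statement about risk.

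**Working it through.** **1. The plan's own figure.** Sample size gives 219 grafts per group for 80% versus 90% patency, 80% power and 5% significance (taken as two-sided).
- Uncorrected: n = [1.96·√(2·0.85·0.15) + 0.8416·√(0.80·0.20 + 0.90·0.10)]² / 0.10² = 198.96, so 199.
- Continuity-corrected: (198.96/4)·[1 + √(1 + 4/(198.96·0.10))]² ≈ 218.5, so 219.
- 219/2 rounds up to 110 patients per group, raised to 125.

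The figure reproduces. It powers the treatment comparison of graft patency and no predictive aim.

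**2. The preoperative contrast.** Inputs are the numbers randomised (Design and randomization procedure) and the group's observational cohort (Background: 87 of 200 patients hypercoagulable; 30-day infarction, stroke or death 17.2% versus 6.6%).
- Randomised hypercoagulable patients: 125 + 125 = 250.
- Randomised normocoagulable patients described: 0.

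The contrast cannot be estimated at any sample size. For scale only, the same uncorrected formula at 17.2% versus 6.6% gives [1.96·√(2·0.119·0.881) + 0.8416·√(0.172·0.828 + 0.066·0.934)]² / 0.106² ≈ 145.3, so 146 per group. With 250 hypercoagulable patients, about 110 normocoagulable patients would be needed for 80% power.

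**3. The order of marker and outcome.**

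| Item | Time | Where stated |
|---|---|---|
| First TEG and Multiplate sample | Day before surgery | Design and randomization procedure |
| Aspirin restarted | Within 24 hours of surgery | Description of medical intervention |
| Clopidogrel started | Day 2 | Description of medical intervention |
| First postoperative sample | Day 4 | Design and randomization procedure |
| Last sample and MSCT | Three months | Design and randomization procedure |
| Outcome period | Surgery to three months | Outcome measures; Data collection |

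The preoperative sample cannot by itself measure a surgically induced change. Nor can it measure reactivity on the trial's treatment, since Perioperative anticoagulation says both drugs are routinely stopped five days before surgery. The usable readings are Day 4 and three months. Events before Day 4 precede the first, and events before the three-month visit precede the second. Early occlusion is expected: the Background names thrombosis as the main cause of vein graft occlusion in the first days and weeks. MSCT is done once, so the date of an occlusion is unknown.

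**4. Illustrative size.** Expected events if the 17.2% rate applied: 0.172 × 250 = 43. The share before Day 4 is not in the documents, so the shares below are assumptions.

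| Assumed share before Day 4 | Events before the reading | Events after it |
|---|---|---|
| 10% | 4.3 | 38.7 |
| 25% | 10.75 | 32.25 |
| 50% | 21.5 | 21.5 |
| 75% | 32.25 | 10.75 |

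**The case against.** **The predictive sentence is closing prose.** Neither the research questions under Hypothesis nor the listed outcomes compare hypercoagulable with normocoagulable patients. The Background puts the TEG question properly, as the extent of the postoperative rise in patients already hypercoagulable. This stands in part. A reader might infer that the trial can say nothing about TEG as a predictor, and that goes too far: the degree of rise, and MA as a continuous measure above 69 mm, both vary within the cohort. The overreach is in the word for the preoperative period in the Conclusions. The benefit statement is a hypothesis explaining the choice of population, and no listed analysis depends on it. It still cannot be confirmed by this design.

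**A normocoagulable cohort may exist.** The flow chart is not shown, Table 1 has no TEG criterion, the interim analysis is timed by hypercoagulable patients, and the MSCT readers are blinded to coagulation status as well as to allocation. An unrandomised cohort cannot be ruled out, and prediction does not need randomisation. But no such cohort is described. It would lie outside the randomised comparison and could not show who benefits most.

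**Timing rules belong in an analysis plan.** A reader might infer that the plan will use the three-month reading as a predictor. Outcome measures names no reading, and the Background gives the purpose of the Multiplate monitoring largely as describing reactivity patterns. So this is a risk in the design as written, not a proven analysis error. It remains worth raising because the stated sampling times and outcome period produce the reversed order unless a rule prevents it.

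**The event count is weak.** This stands. The 17.2% is a 30-day rate for a different composite, taken from 87 observational patients, and half the trial receives clopidogrel. The documents give no share of events before Day 4, and they do not show that an early infarction or a transfusion alters the markers.

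**Conclusion.** The point holds within these limits. In the randomised cohort as described, preoperative hypercoagulability is constant as a yes/no status. It cannot be tested as a predictor of events and death, and a greater benefit in this subgroup cannot be shown. That follows from the entry condition alone and needs no assumption beyond the article's own description of who is randomised.

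For secondary outcomes 2 and 3, events before Day 4 precede every postoperative reading, and events before the three-month visit precede the last one. How many are affected cannot be derived. About 43 events in total is an order of magnitude that rests on carrying over the earlier cohort's rate, and any split by Day 4 is assumed.

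The randomisation, the sample size and the primary comparison of graft patency are unaffected. The changes should be made, but they concern the interpretation of the results and two secondary analyses.

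**What to change.** 1. **Conclusions and Discussion.** Limit the claim to the effect of adding clopidogrel to aspirin in patients above the MA entry threshold. Remove preoperative status from the predictive statement, and keep the greater-benefit statement only as a rationale that this trial does not test. Describe any preoperative TEG association as continuous MA within the enrolled range.
2. **Secondary outcomes 2 and 3, clinical events.** Name the Day 4 reading as the marker. Start the analysis at that sample: include patients alive and event-free then, count only later events, and adjust for treatment arm. Report how many patients are left out because of an earlier event, death or a missing sample.
3. **Three-month reading.** Use it to describe TEG and platelet reactivity over time, not to predict events.
4. **Graft occlusion in outcome 2.** A landmark cannot solve this, because the onset is unknown at the single three-month MSCT. Report the relation to the Day 4 reading as an association only.

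The cost is wording and a later start for two secondary analyses. No extra patients, visits or samples are needed, and inclusion is still open with 135 randomised. The downside is fewer events: on the assumed shares above, between about 39 and 11 of 43 would remain.

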## Trial status

Currently 135 patients are randomized in this trial, and inclusion is ongoing.

## Abbreviations

ADP: Adenosine diphosphate; CABG: Coronary artery bypass grafting surgery; CAPRIE: Clopidogrel versus aspirin in patients at risk of ischemic events trial; CASCADE: Clopidogrel after surgery for coronary artery disease trial; CRF: Case report form; CURE: Clopidogrel in Unstable angina to prevent recurrent ischemic events trial; EUDRACT: European Union Drug Regulating Authorities Clinical Trials; LAD: Anterior descending artery; LIMA: Left internal mammarian artery; LMWH: Low-molecular-weight heparine; MA: Maximal amplitude; MSCT: Multislice computed tomography; NSAIDs: Non-steroid anti-inflammatory drugs; PAPA-CABG: The Preoperative aspirin and postoperative antiplatelets in coronary artery bypass grafting; PCI: Percutaneous coronary intervention; SAE: Serious adverse event; SVG: Saphenous vein graft; TEG: Thrombelastography.
